**4.8 Sampling**

To ensure a diverse range of schools and CYP are included in the feasibility trial, we propose purposeful maximum variation sampling. This is widely used in research to pragmatically identify and select participants that are effective in addressing the research aims, while also maximising diversity and limiting bias.^39^ The key characteristics we would seek variation on include: rural/urban status, proportion of ethnic minority pupils, schools’ deprivation levels (IDACI), schools’ academic achievement (proportion of pupils achieving benchmarks GCSE grades). To ensure we achieve this, we have allocated dedicated time in the project plan during the setup phase to collate school data (publicly available), approach and build relationships with schools who do not typically engage in research, and ensure buy-in from the senior leadership teams (via the collaborators). Both Principal Investigators have expertise in involving diverse communities in research programmes and have started this process during the pilot study.

*Sample size calculation:* As this is a feasibility study, a sample size calculation is not needed. In line with similar work,^26-28^ we will recruit 6 schools to provide sufficient variety of schools and pupil numbers in which to test recruitment, retention and acceptability of the intervention, and feasibility of the research design for evaluation. This is based on the assumption of a potential attrition rate of 50% at T3 (the primary outcome point for Reframe IT-UK). This is common for feasibility trials,^40^ realistic in terms of recruitment, and would allow adequate precision in estimating rates (e.g., attrition, adverse events) relevant to trial outcomes.^40^ This would allow an overall attrition rate of 50% to be estimated with 95% confidence intervals of +/- 12% or, 16% for a single arm. This sample size is also adequate for estimating relevant analysis parameters such as the standard deviation of effects, which are needed for determining the feasibility of a later efficacy trial.^40,41^ Based on findings from the pilot study, we anticipate that 10% of pupils will score in the at-risk range in the screening and will thus be eligible for Reframe IT-UK.

We will monitor recruitment rates from the different methods and associated costs by collecting data on:

1. The proportion of eligible young people who consented;
2. The number of participants recruited during the recruitment stage of feasibility compared with the target;
3. Assessment of contamination of MAPSS programme in control schools;
4. Assessment of CYP satisfaction with intervention and outcome measures.

This will provide evidence on recruiting to trials in school settings, as well as informing the full trial design.

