**4.6 Study Population**

Participants will include Year 10 pupils (aged 14-15). Opt-out ethical procedures will be used – these have been approved by the university research ethics committee in the pilot study and were acceptable to parents and schools. We will utilise purposeful maximum variation sampling to recruit schools in different areas across the region and to ensure inclusivity of diverse populations (e.g., rural/urban, ethnic minority groups, differing deprivation levels, differing academic achievement levels). We will work with partners across the region who can support with this (e.g., Papyrus, Cheshire and Merseyside Safeguarding Group).

The sample will consist of ~810 adolescent pupils in Year 10, recruited from 6 mainstream secondary schools across Cheshire and Merseyside. Six schools will be randomly assigned to one of two arms as part of a cluster-RCT: intervention (n=4) or control arm (n=2). Year 10 pupils in the intervention schools will receive: 1) suicide prevention lesson (n~540 pupils); and 2) pupils scoring 21 or above on the SIDAS^33^ or indicating past suicide ideation will also be offered Reframe IT-UK plus TAU (n~54 pupils). Those in the control arm will receive TAU only (n~27 pupils).

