**4.12 Data and Statistical Analysis**

***Quantitative Data Analysis***

Changes in primary and secondary outcomes over time will be assessed for pupils clustered within schools and the treatment group included as a fixed factor. The analysis will adopt the intention-to-treat approach. As a secondary analysis, compliance (as measured by the number of modules completed) and other potential covariates (e.g., gender) will be accounted for. If the amount of missing data is non-trivial, multiple imputation will be used. We will follow the recently published extension to CONSORT^42^ when reporting the results of this feasibility trial. We will calculate and present in a CONSORT flow chart:

- - 1. The proportion of young people with suicide ideation consenting to the study;
    2. The proportion completing baseline assessment and entering the randomised phase;
    3. The number of online modules used and the proportion completing all sessions;
    4. The proportion completing follow-up assessments at 12-weeks and one-year post-randomisation.

As this is a feasibility study, no formal hypothesis testing will take place. Quantitative data will be reported using summary statistics and 95% confidence intervals. We will compare the continuous scores on the SIDAS outcome measure graphically to assess between group trends. The SD of the primary outcome will inform the sample size calculation for the large-scale RCT.

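### Section 4.8's single-arm precision of 16% fits neither arm of the planned 54/27 split: simple half-widths are about 13% (intervention) and 19% (control)

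*Protocol*

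**What the plan says.** Section 4.8 says that a feasibility study needs no sample size calculation and that six schools give enough variety. It then adds a precision argument. This rests on the "assumption of a potential attrition rate of 50% at T3 (the primary outcome point for Reframe IT-UK"), and concludes that the design permits an "overall attrition rate of 50% to be estimated with 95% confidence intervals of +/- 12% or, 16% for a single arm". The same paragraph calls the resulting precision adequate for rates such as attrition and adverse events. It gives no denominator, ICC or design effect for the two half-widths.

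The numbers of pupils are given elsewhere:

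- Section 4.6: "The sample will consist of ~810 adolescent pupils in Year 10".
- Section 4.8: "we anticipate that 10% of pupils will score in the at-risk range in the screening".
- Section 4.6, intervention arm: at-risk pupils "will also be offered Reframe IT-UK plus TAU (n~54 pupils").
- Section 4.6, control arm: "Those in the control arm will receive TAU only (n~27 pupils").
- Section 4.9: schools are the unit of randomisation, allocated 2:1, four to intervention and two to control.

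Section 4.12 recognises the clustering in the analysis: "Changes in primary and secondary outcomes over time will be assessed for pupils clustered within schools".

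**The concern.** With 2:1 allocation the arms differ in size by a factor of two, so one half-width cannot describe both. The quoted 16% would need about 38 pupils, and neither arm is planned to have that number.

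The sentence is the only quantitative basis for calling the precision adequate. Precision also matters to the study's own purposes. Section 4.1 lists the precision of key parameter estimates among the feasibility indicators, and section 4.12 commits to reporting 95% confidence intervals. A team planning the definitive trial from the 16% would expect more from 27 control pupils in two schools than they can give.

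**Working it through.** **Inputs.** Attrition rate p = 0.50 and 95% confidence (section 4.8). At-risk pupils: 10% of about 810 = 81, split 54 and 27 (sections 4.6 and 4.8). Six schools, 4 and 2 (sections 4.6 and 4.9), so 81/6 = 13.5 at-risk pupils per school. The ICC is not stated, so any value below is an assumption.

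**Step 1: what the stated figures imply.** The simple half-width is h = 1.96 × √(0.25/n), so n = 0.25 × (1.96/h)².

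- h = 12%: n = 66.7 (61.5 to 72.6 allowing for rounding).
- h = 16%: n = 37.5 (35.3 to 40.0 allowing for rounding).

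With equal arms, a total of 72 (36 per arm) reproduces the pair: 11.5% and 16.3%. No 2:1 split does. For any total, and any design effect common to both arms, the ratio of arm to overall half-width is √1.5 = 1.22 for the larger arm and √3 = 1.73 for the smaller. The stated ratio is 16/12 = 1.33, and rounding allows only 15.5/12.5 = 1.24 to 16.5/11.5 = 1.43. Equal arms give √2 = 1.41.

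**Step 2: the planned numbers, no clustering.**

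| Group | n | 1.96 × √(0.25/n) | Stated |
|---|---|---|---|
| Overall | 81 | 10.9% | 12% |
| Intervention | 54 | 13.3% | 16% |
| Control | 27 | 18.9% | 16% |

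**Step 3: other interval methods.** Across Wald, continuity-corrected, Wilson, exact, Agresti-Coull and t-based intervals, n = 54 gives 12.9% to 14.3% and n = 27 gives 17.6% to 20.7%. None gives 16% for either arm. The overall 12% can be reached by rounding, since n = 81 with a continuity correction gives 11.5%.

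**Step 4: other denominators.** All pupils (810, 540, 270) give 3.4%, 4.2% and 6.0%. Halving the at-risk numbers for the assumed loss (40.5, 27, 13.5) gives 15.4%, 18.9% and 26.7%. Neither set reproduces the pair.

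**Step 5: could clustering explain it?** The design effect is 1 + (13.5 − 1) × ICC. Reaching 12% from 81 needs an ICC of about 0.017, and 16% from 54 needs about 0.035. Reaching 16% from 27 needs a design effect of 0.72, below 1. No single ICC gives both stated figures.

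**Step 6: illustrative effect of clustering (assumed ICC).**

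| ICC | Design effect | Overall | Intervention | Control |
|---|---|---|---|---|
| 0.02 | 1.25 | 12.2% | 14.9% | 21.1% |
| 0.05 | 1.625 | 13.9% | 17.0% | 24.0% |

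These use 1.96 as the multiplier. The control column is optimistic because it rests on two schools: a t multiplier with 1 degree of freedom is 12.7.

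**The case against.** The strongest reply is that little depends on this sentence. The protocol disclaims a sample size calculation, section 4.12 rules out formal hypothesis testing, and the retention rule in section 4.1 and the T3 attrition bands in section 4.2 are not set by arm. Correcting the figures changes no number of schools or pupils and no progression threshold. That stands, and it limits the point to the precision statement. For adverse events the 50% rate is also the worst case: at a 10% rate, 1.96 × √(0.09/n) gives 6.5%, 8.0% and 11.3% for n = 81, 54 and 27.

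It can also be said that the single arm is not named. Reframe IT-UK is given only in the intervention arm, and on that reading 16% is conservative against 13.3% and lies within the illustrative clustered range of 14.9% to 17.0%. This is fair, but the sentence does not limit itself to one arm, and for the control arm 16% is too favourable under every method tried.

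Several stronger inferences are tempting, but the documents do not support them:

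- *That clustering was ignored.* This would be inferred only from the absence of an ICC. Section 4.12 does recognise clustering, and the size of its effect here is an assumption.
- *That the overall 12% is wrong.* It exceeds the simple 10.9% and agrees with a small ICC (12.2% at 0.02).
- *That the control half-width is at least 19%.* The 18.9% is a rounded simple value, and Wilson gives 17.6%. About 19% before clustering is as far as one can go.
- *That the figures were taken from a 1:1 trial of 72.* That is back-solving, and it is not the only solution. For example, 38 intervention pupils with all 27 controls (65 in total) would give 1.96 × √(0.25/65) = 12.2% and about 16% for the 38. The protocol states neither basis, and the second would still leave the control arm at about 19%.

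**Conclusion.** The point holds for the single-arm figure. With 54 and 27 at-risk pupils, 16% overstates the intervention arm's simple half-width by about 3 percentage points (13.3%) and understates the control arm's by about 3 (18.9%; about 2 to 5 across interval methods). This rests on reading the T3 attrition rate as that of the at-risk pupils, which section 4.8 supports by tying it to Reframe IT-UK. The all-pupil reading fits far worse.

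The overall figure can be defended, but its denominator should be named. Any positive ICC widens all three figures. The illustrative ranges for ICC 0.02 to 0.05 are 12% to 14% overall, 15% to 17% intervention and 21% to 24% control. They show direction and rough scale and are not estimates. A reader should not infer that the study is the wrong size. The fault is a stated precision that the design does not deliver by arm.

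**What to change.** In section 4.8, replace the precision sentence with wording such as: *about ±11% overall (n=81), ±13% in the intervention arm (n=54) and ±19% in the control arm (n=27) before allowing for clustering by school, which will widen these*. If ICC-based figures are added, mark them as illustrative, state the assumed ICC and the 13.5 at-risk pupils per school, and say that the control figure rests on two schools. Qualify the claim of adequate precision for the control arm. If the authors used different denominators, such as an assumed uptake of Reframe IT-UK, they should state them and derive the half-widths from them.

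The cost is a sentence or two of protocol text and a less favourable stated precision for the control arm. No extra pupils or schools are needed, and no progression criterion changes.

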**4.9 Randomisation**

The unit of randomisation is the schools. After baseline data collection is complete, 6 schools will be randomised to one of two study groups. We will be comparing both arms to test which, if any, is better. To create balance in terms of deprivation, ethnicity, rurality and educational outcomes, a minimisation algorithm will be used at an intervention-to-control ratio of 2:1 across Cheshire and Merseyside. Two schools will be allocated to the control arm and four schools will be allocated to the intervention arm by a university statistician, who is independent of the study and blind to school identities. Methods of allocation concealment and randomisation processes will follow CONSORT^42^ (see figure 1). Schools will be randomised to receive a suicide prevention lesson (e.g., safeTALK) and Reframe IT-UK and TAU, or TAU only, via a random sequence generation computer algorithm. The method of randomisation will be conducted using a routine within STATA to generate (stratified) randomised (block sizes of 2, 4 and 6) allocations. Researchers completing study assessments will be masked to intervention allocation. The trial will follow an Intent-To-Treat (ITT) protocol. Attrition will be recorded and reasons for drop-out recorded where possible. Guidance will be sought from the advisory groups on how to manage and minimise attrition over the study period.

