**4. Research Plan/Methods**

**4.1 Design and Theoretical/Conceptual Framework**

The study will be conducted over a 2-year period (Jan 2024-Jan 2026), with 3 months for set up, 18 months feasibility, and 3 months consolidation.

This study adopts a multiphase feasibility design, consisting of 3 work packages (WP):

**WP1:** A three-month set-up stage to: i) make any adjustments to the interventions as determined from the pilot study, ii) recruit the RA, and iii) spend dedicated time recruiting schools from a diverse range of backgrounds, with two schools recruited in the first 3 months and the remaining four schools within 9 months, to enable alignment with school academic terms.

**WP2:** An 18-month feasibility study evaluating MAPSS in 6 schools: a feasibility cluster-RCT (schools as the unit of randomisation). Four schools will be randomised to receive MAPSS (intervention arm) and two schools will be randomised to continue with usual practice (control arm). Surveys will be completed by both arms at all timepoints. The trial will include i) baseline survey, ii) universal suicide prevention lesson (e.g., safeTALK) in intervention arm, iii) survey and screening 2 weeks after suicide prevention lesson, iv) an indicated Reframe IT-UK CBT intervention in intervention arm for pupils identified as high suicide risk, and usual care in control arm v) survey 2-weeks after Reframe IT-UK CBT, vi) survey 12-months post baseline.

**WP3.** A parallel process evaluation, to establish perceptions of social validity of the programme for use in the UK, and the appropriateness of the research design for effectiveness trials.

The study is facilitated by an extensive partnership with Local Authorities, schools, public advisors, professional educators, and researchers (see Letters of Support attached from collaborators and partner organisations). The specific objectives are to assess:

1. The acceptability and safety of a suicide prevention programme in schools

A mixed-methods approach will be used to determine acceptability and safety of trialling a suicide prevention programme in UK schools. The proportion of pupils who complete all agreed sessions of therapy will be recorded (>60% excellent; 40%-60% acceptable; <40% not acceptable).

Safety will be operationalised in terms of adverse events linked to the intervention (e.g., suicidal behaviour, crises, or increased self-harm), and in terms of self-reported adverse consequences at post-intervention assessments.

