**4.4 Control/Comparator Group**

Participants in schools randomised to the control group will receive treatment as usual (TAU; e.g., from the school nurse or external mental health services), based on the typical provision at each school. The pastoral staff will be asked to record what TAU comprises in each school through the completion of a ‘usual practice’ survey prior to randomisation and at T4, to establish programme differentiation, any changes over time, and to control for any compensatory rivalry that may occur over the course of the trial. To ensure safety and appropriate support in the event of pupils being flagged as at-risk in the control group, schools who do not engage with the SP-OT (suicide prevention training for designated teachers in recruited schools) training will be unable to progress through the trial.

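### Section 4.9 names two incompatible ways of allocating the six schools, and block sizes of 2 and 4 cannot hold the stated 2:1 ratio

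*Protocol*

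**What the plan says.** All the allocation rules stand in one paragraph, Section 4.9 (Randomisation) of the protocol.

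- **Aim.** The purpose is stated as "To create balance in terms of deprivation, ethnicity, rurality and educational outcomes".
- **Method.** The means given for this is minimisation: "a minimisation algorithm will be used at an intervention-to-control ratio of 2:1 across Cheshire and Merseyside".
- **Arm sizes.** "Two schools will be allocated to the control arm and four schools will be allocated to the intervention arm". The allocation is made by an independent statistician who does not know which school is which. The same four-and-two split appears under WP2 in Section 4.1 and in Section 4.6.
- **Method, described again.** A Stata routine will "generate (stratified) randomised (block sizes of 2, 4 and 6) allocations". No strata are named, and no ratio within blocks is given.
- **Timing.** "After baseline data collection is complete, 6 schools will be randomised to one of two study groups".

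Two statements elsewhere bear on how this would be carried out. Section 4.1 has "two schools recruited in the first 3 months and the remaining four schools within 9 months". Section 4.4 says that schools not engaging with the staff course (SP-OT) "training will be unable to progress through the trial", without saying whether this is settled before allocation.

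**The concern.** Minimisation and stratified permuted blocks work differently. Minimisation assigns each school by looking at the imbalance among schools already assigned. Permuted blocks draw from a list prepared in advance, separately within each stratum. A statistician handed this paragraph cannot carry out both, and nothing in it says which takes precedence.

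The block sizes make matters worse, because two of the three cannot produce the ratio stated a few sentences earlier. The list 2, 4, 6 is a usual choice for 1:1 allocation and looks as if it came from such a design.

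At stake is an allocation that cannot be redone once schools have been told. With two control schools, each is half of its arm. The study is also meant to show that a cluster-randomised design is workable for a definitive trial, and its allocation is to be reported to CONSORT standards. That is not possible while two methods are specified.

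**Working it through.** **Inputs.** Six schools; ratio 2:1; four intervention and two control; balancing factors deprivation, ethnicity, rurality and educational outcomes; block sizes 2, 4 and 6. All are from Section 4.9, with the arm sizes repeated in Sections 4.1 and 4.6.

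**Step 1: reproduce the stated split.** 6 × 2/3 = 4 and 6 × 1/3 = 2. The four-and-two split agrees with 2:1.

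**Step 2: test each block size at 2:1.** A block of size b needs b × 2/3 intervention and b × 1/3 control places, both whole numbers, so b must be a multiple of 3.

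| Block size | Intervention | Control | Possible at 2:1? |
|---|---|---|---|
| 2 | 1.33 | 0.67 | No |
| 4 | 2.67 | 1.33 | No |
| 6 | 4 | 2 | Yes |

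A block of 2 and a block of 4 could total 4:2 only with different ratios in the two blocks, for example 1:1 followed by 3:1. That is not a 2:1 block scheme, and the protocol describes nothing of the kind.

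**Step 3: what the listed sizes give at 1:1, the ratio they suit.** The sequences that fill six places exactly are 2+2+2, 2+4, 4+2 and 6. Each gives 3:3. If each block size is equally likely (an assumption) and the last block may be left unfinished, 3:3 has probability 0.85, and 4:2 and 2:4 have 0.08 each. The protocol does not say the blocks are 1:1; this shows only what a routine set up in the usual way for these sizes would do.

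**Step 4: stratification.** The protocol names no strata. If the four balancing factors were used as strata, each with two levels (both assumptions), there would be 2 × 2 × 2 × 2 = 16 cells for 6 schools. At least 10 cells would be empty and most or all of the rest would hold a single school, so blocks within cells could not deliver the intended balance.

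**Step 5: size of the allocation space.** The number of ways to choose two control schools from six is C(6,2) = (6 × 5)/2 = 15. All can be listed and checked for balance by hand.

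**Step 6: recruitment waves.** Section 4.1 brings schools in as two and then four. Neither number is a multiple of 3, so neither wave can be split 2:1 by itself. Any scheme must run across both waves.

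**The case against.** The strongest reply is that the intended result is not in doubt. The protocol states 2:1 and four against two in three sections, nowhere mentions 1:1, and lists a block size, 6, that yields exactly 4:2. An independent statistician would notice the problem and settle it. The study tests no hypotheses formally (Section 4.12), so the harm is limited. This stands as far as it goes: the consequence is an unworkable instruction, not a wrong arm size already built into the trial. It does not remove the contradiction, and a later analysis plan could not either without overruling a sentence of the protocol.

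Three stronger readings are tempting, and the protocol does not support them.

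- A reader might infer that the trial will end up at 3:3, with about 405 pupils receiving the lesson (3 × 135) instead of about 540, and about 40 at-risk pupils per arm instead of 54 and 27. That requires 1:1 blocks, which the stated ratio and arm sizes exclude.
- A reader might infer that the timing is contradictory, because schools join months apart but six are randomised after baseline. Section 4.1 staggers recruitment, and the sentence on baseline can be read school by school, which suits minimisation. This is unclear wording and no more.
- A reader might infer that the SP-OT rule removes schools after allocation and so breaks intention-to-treat. Section 4.3 says the training equips staff to handle risk found by screening, screening is part of every survey including baseline, and allocation follows baseline. The natural order is therefore training before allocation. The protocol should say so, but it describes no exclusion after allocation.

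**Conclusion.** The point holds in two parts. Section 4.9 specifies two allocation methods that cannot both be used, and two of its three block sizes are arithmetically incompatible with its own 2:1 ratio. Neither part rests on an assumption.

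The further statements are conditional. The 3:3 result assumes 1:1 blocks, and the 16 cells assume that the four factors serve as two-level strata. They show why the block sentence should not survive; they do not predict what will happen. The order of baseline survey, SP-OT engagement and allocation needs clarifying and is not an error.

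The paragraph is wrong as written and needs correcting before any school is randomised.

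**What to change.** Delete the wording on stratification and on blocks of 2, 4 and 6, and state one method that guarantees four intervention and two control schools. Any of these would do:

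- **Minimisation** on the four named factors, with a random element, constrained to finish at 4:2. This is closest to the present text and copes with schools joining at different times.
- **Constrained randomisation**, if all six schools can be allocated together. List the 15 possible allocations, keep those acceptably balanced on the four factors (Section 4.8 notes that school data are publicly available), and draw one at random. Set a minimum number of retained allocations beforehand so that the draw stays random.
- **Blocks**, if they are preferred: multiples of 3 only and unstratified, meaning one block of 6 or two of 3. This gives the ratio but does not by itself balance the four factors.

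In the same edit, say that SP-OT engagement is confirmed before a school is allocated, and that each school is told its arm only after its own baseline survey.

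The cost is one reworded paragraph and little programming. Allocating all six together may make early schools wait. If baseline were held to the end of month 9 (September 2024), the one-year survey would fall at about the end of September 2025, roughly two months before follow-up closes in November 2025 (Section 6). If that is too tight, minimisation avoids the wait.
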